## Abstract

Exposure to ionizing radiation (IR) is inevitable in various X-ray imaging examinations, with computed tomography (CT) being a major contributor to increased human radiation exposure. Ionizing radiation may cause structural damage to macromolecules, particularly DNA, mostly through an indirect pathway in diagnostic imaging. The indirect pathway primarily involves the generation of reactive oxygen species (ROS) due to water radiolysis induced by IR, leading to DNA damage, including double-strand breaks (DSB), which are highly cytotoxic. Antioxidants, substances that prevent oxidative damage, are proposed as potential radioprotective agents. This *Study Protocol* article presents the rationale for selecting vitamin C as a preventive measure against CT-associated IR-induced DNA damage, to be investigated in a randomized placebo-controlled trial, with a full in vivo design, using an oral easy-to-use schedule administration in the outpatient setting, for the single CT examination with the highest total global IR dose burden (contrast-enhanced abdomen and pelvis CT). The study also aims to explore the mediating role of oxidative stress, and it has been written in adherence to the Standard Protocol Items recommendations.

## 1. Introduction

### 1.1. Ionizing Radiation in Medical Imaging: Computed Tomography and Patient Dose

Radiation encompasses any moving form of energy. It is categorized into ionizing and non-ionizing forms. Ionizing radiation (IR) is further classified into high and low linear energy transfer radiations. The latter, electromagnetic radiations (X-rays and γ radiation), travel as waves that easily penetrate body tissues [1,2]. In particular, X-rays have become increasingly used to reveal anatomy and internal organs for medical purposes (Figure 1).

The average background radiation remains steady at 3 millisieverts (mSv) per year and has shown minimal change over the past three to four decades [3]. However, total global per capita radiation exposure doubled until 2010, largely attributed to the increasing radiation from medical sources [3,4]. The escalating doses associated with computed tomography (CT) scans have been identified as the primary driver [3]. In the United States in 2016, 230 CT scans per 1000 people were conducted, with abdomen and pelvis scans comprising the largest category (~20 million) [5,6]. Yet, a recent global assessment (2009–2018) indicated a greater CT increase in other countries [5]. While annual background radiation is ~3 mSv, a whole-body CT scan exposes individuals to approximately 10 mSv [1,7]. 

For CT, radiation exposure is quantified with CT dose index-volume (CTDIvol) and dose-length product (DLP) [3]. However, they do not provide an accurate patient dose estimate [8,9] because they do not consider how much absorbed radiation dose biologically affects tissues [1]. Patient dose estimates need to consider standard-sized patient region-specific “k factors” [8,9,10,11,12], which can then be adjusted for specific patient size and shape [9,13,14,15]. The patient dose estimate termed effective dose (ED) is endorsed by the International Code of Radiology Practice for dosimetry in diagnostic radiology [16], as it was long developed by the International Commission on Radiological Protection [17].
Effective dose (ED) = DLP × *k* factor (corrected for specific-patient size)

DLP, scan region, and patient size enable the estimation of effective dose (ED), which is the preferred radiation quantification parameter for assessing the individual patient effects of CT-related IR exposure. For abdomen and pelvis CT, additional adjustments considering abdominal fat may enhance the precision of ED estimation [18].

### 1.2. Ionizing Radiation and DNA Damage: Indirect Mechanism through Oxidative Stress

The notion of genetic material impairment resulting from ionizing radiation (IR), such as chromosome breakage, precedes our comprehension of DNA’s structure [19]. Initially, a direct pathway implicating collisions between high-energy particles or photons and DNA strands was proposed. However, an oxidative stress (OS)-mediated indirect mechanism of IR-induced DNA damage was later described, accounting for the majority (60 to 70%) of the total DNA damage induced by IR [20,21,22,23,24]. OS occurs due to an imbalance between the production of oxidant species and the activity of the antioxidant system, which favors the first. This OS-mediated indirect mechanism was described as generating reactive oxygen species (ROS) via IR-induced water radiolysis (Figure 2).

Within a fraction of a second (10^−15^ to 10^−6^ s), IR promotes the release of electrons, triggering homolytic cleavage of covalent bonds, which generates free radicals and ROS. While the direct pathway leads to immediate DNA damage, and the indirect pathway leads to DNA damage both immediately and over varied timeframes, DNA damage occurring after the first second of post-exposure contributes to total DNA damage in a significantly minor proportion, with previous studies showing that DNA damage increases within the first 5 min post-exposure and thereafter it decreases [25]. This evidence is in line with the notion that experiments assessing DNA damage should take care to avoid repair of strand breaks [26], providing the rationale to propose that DNA damage induced by IR may be assessed with 5 min interval post CT. Some ROS are consumed in neutralizing reactions, but those present in the cellular nucleus often engage in propagation reactions, potentially leading to DNA damage, including double-strand breaks (DSBs) [20,21,22,23,24,27,28,29,30], which are considered the most relevant and cytotoxic lesions. If not repaired or repaired incorrectly, they can cause structural chromosomal abnormalities, possibly initiating mutations and thereby contributing to carcinogenesis [31,32,33]. Phosphorylation of the histone variant H2AX is one of the initial steps in the cellular response to DSBs. Hence, the immunofluorescence analysis of this phosphorylated histone, i.e., γ-H2AX, is widely used to monitor IR-induced DNA damage [34]. 

### 1.3. Antioxidant Defense System: Exogenous Antioxidants against IR-Induced Oxidative Stress

Antioxidants are substances that delay, prevent, or eliminate oxidative damage to target molecules [35,36,37]. Endogenous antioxidants serve as the primary defense against OS by effectively neutralizing ROS [38,39]. Under conditions of heightened ROS levels, however, endogenous defenses may be overwhelmed, resulting in OS [38,40]. In such cases, exogenous antioxidants can bolster overall antioxidant defense [38,41], being proposed as radioprotective agents through various mechanisms [28]. The mechanisms involved in IR-induced DNA damaging and repairing by different radioprotectants have been previously revised and detailed, with existing research suggesting that free radical scavenging and induction of enzymatic endogenous antioxidants may play a significant role against most of the IR-induced indirect DNA damage [37] (for a comprehensive overview on proposed effects and mechanisms of different radioprotective agents, we underscore the in-depth literature review article by Smith et al. [28]). Thus, biomarkers of the antioxidant capacity (e.g., ferric reducing ability of plasma; FRAP assay [42]) previous to exposure may be associated with IR-induced DNA damage. 

Vitamin C has been described as one of the most potent antioxidants and can prevent IR-induced DNA damage through direct and indirect antioxidant mechanisms [37,43,44]. Directly, it eliminates ROS due to its electron-donating capacity, which allows it to oxidize to dehydroascorbate [37]. At certain plasma concentrations, it also alters the reaction between the superoxide anion and nitric acid [45,46]. Indirectly, vitamin C inhibits ROS-producing enzymes and inflammatory responses via NF-κB pathway inhibition [38,47]. It prevents the OS-enhancing effect of endothelial nitric oxide synthase by stabilizing tetrahydrobiopterin [38,46,48]. It also enhances the effect of other antioxidants, such as recycling alpha-tocopherol [37,49]. A recent and growing body of evidence from experimental studies with different designs (i.e., in vitro, in vivo, or mixed in vitro/in vivo) supports vitamin C as a novel antioxidant intervention to reduce IR-induced DNA damage in patients undergoing CT imaging (Supplementary Materials) [50,51,52,53,54,55]. 

Beyond vitamin C, previous in vitro studies [52,55] have also compared different antioxidants, showing that vitamin C and NAC had the highest significant reduction of the excess DNA damage induced by IR. In the clinical setting [51], the effect of vitamin C was two-fold higher than that of NAC, even administered minutes prior to IR exposure, which is an important consideration under the light of time-setting data showing that the effect of NAC increases until its peak at minute ~30, with a steeper curve than vitamin C, which reaches its peak at minute ~60 (which provides a rationale to propose that supplementation strategies may maximize its impact at around 60 min post-intervention). Yet, aiming for wide clinical use and a high impact on total global IR dose burden, intravenous administration strategies may limit its clinical application. Moreover, it should also be noted that high-dose antioxidant strategies may lead to counterproductive effects. Whereas DNA protective effects may be observed at vitamin C plasma levels ~50 μmol/L [56], breakage-type chromosomal aberrations may be induced at ~110 μmol/L, of notice, even in non-irradiated cells [57]. Although low oral doses of vitamin C (~600 mg) have shown significant results in a mixed in vitro/in vivo study [53], consistent reduction of excess DNA damage induced by IR is found with intermediate oral doses of ~1 g. It should be underscored that no previous study has performed vitamin C measurements prior to (or after) the supplementation strategy, which is lacking to provide further understanding of how baseline vitamin C levels potentially influence result variability. Provided that low/high doses of vitamin C are avoided, further evaluation of hypothetical increased effects with the addition of other antioxidants could not be consistently provided with current evidence from clinical studies. Yet, a combination of antioxidants showed a 58% reduction of excess DNA damage [34], comparable to the 61% effect size found with intermediate oral doses of vitamin C [54], and in vitro studies have also failed to provide consistent evidence supporting additive effects [52].

Existing literature holds the plea for further investigation into the mediating role of OS previous to exposure in IR-induced DNA damage, particularly focusing on the outpatient setting, with the single CT examination with the highest total global IR dose burden (electromagnetic radiation, i.e., excluding particulate radiation), using the most accurate estimation methods for patient dose. The initial premise that OS plays a significant mediator role in CT-associated IR-induced DNA damage forms the basis for proposing the hypothesis that enhancing antioxidant capacity through an exogenous antioxidant intervention (1 g oral vitamin C, one hour prior to exposure) could offer new interventional opportunities.

### 2.2. Study Population and Recruitment

The study population comprises consecutive patients with health concerns related to the abdomen and pelvis organs and a clinical indication for contrast-enhanced (CE) abdomen and pelvis CT in the outpatient setting, with scheduled appointments at the Radiology Department of the University of Chile Clinical Hospital. Patients will be recruited via telephone call approximately 36–72 h before their appointment. Additionally, non-IR-exposed health-related personnel volunteers and their relatives without an indication of IR-associated examination will be recruited as a control group through a direct onsite invitation from the researchers.

Inclusion criteria: Male and female patients aged 18 to 75 capable of providing a signed informed consent.Exclusion criteria: Pregnant women, severe chronic kidney disease (glomerular filtration rate < 30 mL/min/1.73 m^2^), or contraindications for antioxidants supplementation or iodinated contrast examinations. Genetic syndromes, onco-hematologic diseases or history of peptic ulcers or urinary stones. Occupational exposure to IR; radiation therapy or chemotherapy in the last 6 months, or exposure to other IR-associated examinations in the previous 72 h or immediately after the abdomen and pelvis CT. Use CE CT premedication, antioxidant supplementation regularly or on the day of the CT exam, iron supplementation, or an iron-restricted diet.Sample size: proposed on the basis of other clinical studies to detect a significant reduction of increased DNA damage in the interventional group [50,51,52,53]. Assuming increases in γ-H2AX foci ranging 1–99% (~20% dispersion [59]), a sample size of *n* = 25 patients per group (assuming *n* = 3 missing values), there is an 80% power to detect any mean difference between the placebo and interventional groups > 16%.Study groups: Four groups, A_NONE-NONE_, B_NONE-EXP_, C_PLAC-EXP_ and D_VITC-EXP_, named according to corresponding intervention (none/placebo/vitamin C) and exposure (none/CE abdomen and pelvis CT), as detailed below. For reference on the study subjects’ protocol timeline, please also see Figure 3.
A_NONE-NONE_: Not recipients of any intervention (placebo or vitamin C) nor exposure (CE abdomen and pelvis CT). Blood sample #1 (T_base_) will be collected 60–80 min before blood sample #2 (T_post_), with a clinical interview in between (T_ci_). B_NONE-EXP_: Not recipients of any intervention but exposed (T_exp_). Blood sample #2 (T_post_) will be collected 60–80 min after the blood sample #1, with a clinical interview (T_ci_) followed by the exposure (T_exp_) in between. Based on comparative data with A_NONE-NONE_ (i.e., interim estimates of the exposure effect), re-estimation of the starting sample size (*n* = 25) may be considered for these non-interventional groups [60]. With an estimation of the exposure effect, randomized placebo-controlled enrollment will start for the interventional (C_PLAC-EXP_/D_VITC-EXP_) groups.C_PLAC-EXP_: Recipients of a placebo (T_int_) and exposed (T_exp_). Blood sample #2 will be collected immediately prior to CT. Blood sample #3 (T_post_) will be collected 60–80 min after blood sample #1, with the administration of the placebo (T_int_), clinical interview (T_ci_) and exposure (T_exp_) in between.D_VITC-EXP_: Recipients of the oral vitamin C intervention (T_int_) and exposed (T_exp_). Blood sample #2 will be collected immediately prior to CT. Blood sample #3 (T_post_) will be collected 60–80 min after blood sample #1, with the administration of the vitamin intervention (T_int_), clinical interview (T_ci_) and exposure (T_exp_) in between.

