### 2.6. Statistical Analysis

Continuous variables will be summarized as mean values ± standard deviations if normally distributed and compared with Student’s *t*-tests. Continuous variables will be summarized as median (interquartile ranges) if they are non-normally distributed and compared with Mann–Whitney U-tests. Dichotomous variables will be summarized as percentages and compared using Chi-squared tests. ANOVA tests will be performed to compare changes among the three subgroups. Box and whisker plots will be built to illustrate differences in OS and DNA damage biomarkers. Spearman and linear regression analyses will be performed to evaluate correlations and multivariate associations. Multivariate logistic regression analyses will be performed to evaluate determinants of γ-H2AX foci change. To examine whether the potential association of IR doses with γ-H2AX foci change is mediated by OS biomarkers, mediation analyses will be performed with the method described by Preacher and Hayes [61,62], which allows for testing the significance and magnitude of mediation. In all analyses, a two-sided significance level of *p* < 0.05 will be considered statistically significant. Data will be analyzed using IBM SPSS software version 29 (SPSS Inc., Chicago, IL, USA), STATA 18 (STATA Corp., College Station, TX, USA), and R version 4.3.1 (R Foundation for Statistical Computing, Vienna, Austria).

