Previous clinical studies [51,54] have investigated the hypothesis that an antioxidant intervention may counteract the IR-induced DNA damage without studying OS biomarkers to quantitatively size the mediating effect through this pathway, limiting further understanding of the underlying mechanisms and the overall potential of antioxidant intervention strategies. This is an important distinct methodological feature to aid in proposing further novel approaches. Compared to the study by Stehli et al. [51], which randomized patients to receive an intravenous antioxidant intervention, the current study aims to evaluate a simple oral intervention that may be used routinely in the outpatient setting, further making it unique in terms of its potential clinical impact. Also, the current study is centered on a clinical imaging examination with the most IR patient dose burden according to current international radiation dose estimation data, which is a strength compared to most previous studies in terms of the potential impact of its findings. Departing from a previous clinical outpatient study by Tao et al. [54], the current study proposes the use of patient dose estimates to allow for a comparison of its results with that of further studies on different IR-based clinical imaging examinations associated with stochastic effects in risk estimation fashion according to international recommendations. 

Furthermore, this is the first study to be performed in a multiple-group setting, with either exposure or no exposure, receiving either placebo, the antioxidant intervention or no intervention, each with appropriate statistical power, which is another strength of this study protocol to advance currently available literature. It should also be underscored that our measurements of baseline vitamin C will provide data for the first time to better characterize the clinical need for vitamin C supplementation to counterbalance IR-induced DNA damage. We also expect that the design and execution by a multidisciplinary team will allow a better understanding and more precise quantification of the role of OS mechanisms on the pathways that lead to IR-associated DNA damage, opening new avenues for potential counteracting effects by antioxidant interventions. 

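### The stated 80% power for a 16-point difference is obtained only if all 25 patients per group are analysed, although the same sentence assumes 3 missing values

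*Protocol article*

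**What the plan says.** The sample size item in section 2.2 of the protocol article gives the planning assumption as "Assuming increases in γ-H2AX foci ranging 1–99% (~20% dispersion [59" (the number is a literature citation). It then says that with "a sample size of *n* = 25 patients per group (assuming *n* = 3 missing values), there is an 80% power to detect" a difference, which it specifies as "any mean difference between the placebo and interventional groups > 16" per cent.

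Three other places bear on the calculation:

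- Section 2.6 fixes the test level: "In all analyses, a two-sided significance level of *p* < 0.05 will be considered statistically significant". It names Student's t-test for normally distributed variables and the Mann–Whitney test otherwise.
- Section 2.3 sets 1:1 randomisation between placebo and vitamin C.
- The description of the two non-randomised groups in section 2.2 refers to 25 as the number those groups start with.

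The Discussion (section 3) describes the multiple-group design as "each with appropriate statistical power". The article shows no power calculation other than the one for placebo versus vitamin C.

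**The concern.** A sample size sentence that mentions expected losses should give the power that remains after them. Here the sentence mentions the losses, but its figure matches a calculation in which nobody is lost. The article also does not say whether the 3 missing values are per group or in total, or whether 25 is the number enrolled or the number evaluable.

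This is the only power statement in the article, and it concerns the randomised comparison on the primary outcome, γ-H2AX foci. If the losses occur as assumed, the chance of missing a true 16-point difference is higher than the stated 20%. A null result would then be slightly weaker evidence against an effect of that size than the text suggests.

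**Working it through.** **Inputs**

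- Difference: 16 percentage points in the increase of γ-H2AX foci, placebo versus vitamin C (section 2.2).
- SD: 20 points. The text says dispersion, not SD, so this is an assumption. It is the reading that reproduces the stated figure.
- Two-sided 5% level and t-test (section 2.6); 80% power (section 2.2); 1:1 allocation (section 2.3).
- 25 per group, 3 missing values (section 2.2).

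**Formulas**

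Standard error of the difference: SE = SD × √(1/n₁ + 1/n₂).

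Normal approximation: power = Φ(16/SE − 1.96), and the difference detectable with 80% power = (1.96 + 0.8416) × SE = 2.8016 × SE.

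The t-test values use the noncentral t distribution with noncentrality 16/SE and n₁ + n₂ − 2 degrees of freedom.

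**Step 1: reproduce the plan's figure with no losses**

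- Required n per group, normal approximation: 2 × 2.8016² × (20/16)² = 24.5, rounded up to 25. The t-test gives 25.5.
- With 25 per group: SE = 20 × √(2/25) = 5.657, and 16/SE = 2.828.
- Power = Φ(0.868) = 80.7% (normal), 79.1% (t).
- Detectable difference = 2.8016 × 5.657 = 15.85 (normal), 16.2 (t).

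Both formulas agree with the stated pair of 80% and 16 once rounded, so the plan's figure corresponds to 25 analysed per group.

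**Step 2: 3 missing per group, 22 evaluable**

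- SE = 20 × √(2/22) = 6.030, and 16/SE = 2.653.
- Power = Φ(0.693) = 75.6% (normal), 73.6% (t).
- Detectable difference = 2.8016 × 6.030 = 16.9 (normal), 17.3 (t).

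**Step 3: 3 missing in total, 24 versus 23**

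- SE = 20 × √(1/24 + 1/23) = 5.836, and 16/SE = 2.742.
- Power = Φ(0.782) = 78.3% (normal), 76.5% (t).
- Detectable difference = 2.8016 × 5.836 = 16.35 (normal), 16.7 (t).
- If all 3 fall in one arm (25 versus 22), the results are almost the same: 78.1% and 16.4 (normal), 76.4% and 16.7 (t).

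**Summary (SD 20, two-sided 5%)**

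| Analysed | Power at 16, t | Power at 16, normal | 80% power at, t | 80% power at, normal |
|---|---|---|---|---|
| 25 + 25 | 79.1% | 80.7% | 16.2 | 15.85 |
| 24 + 23 | 76.5% | 78.3% | 16.7 | 16.35 |
| 22 + 22 | 73.6% | 75.6% | 17.3 | 16.9 |

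Compared within one formula, 3 losses per group cost about 5 points of power (79.1 to 73.6 by t-test, 80.7 to 75.6 by normal approximation) and raise the detectable difference by about 1.1 points. Three losses in total cost about 2.5 points of power and 0.5 points of difference.

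**Step 4: could another setting explain the figure?**

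- A one-sided test with 22 per group gives 83 to 84% power and a detectable difference of about 15.0 to 15.2. It does not match, and section 2.6 rules it out.
- With 22 per group, 80% power at 16 points needs an SD of about 18.5 (t) or 18.9 (normal).
- If 28 were enrolled and 25 remained after 3 losses, the stated power would stand.

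**The case against.** The strongest defence is that the inputs are loose and the gap is small. The dispersion is given only as approximately 20%; with an SD of 19 and 22 per group, the normal approximation gives a detectable difference of 16.05, which rounds to the stated figure. If the 3 losses are in total, the normal approximation gives 16.35 points and 78.3% power, also close to the statement. And 25 may be the number left after losses.

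Part of this stands. The article never states 22 evaluable, so the per-group reading cannot be presented as the plan's own number, and the result has to be given as a range. The reading of 25 as net of losses cannot be excluded, although no enrolment of 28 appears. The remark that treats 25 as a starting number speaks against that reading, but it is made about the non-randomised groups. What does not fall away is that, at the SD that reproduces the claim, power at 16 points drops below 80% under either reading of the losses and with either formula.

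On the Discussion's wording, it can be said that equal group sizes and an equal SD would give every pairwise comparison the same detectable difference. That is true as arithmetic, but the article does not state an SD or a target difference for the other comparisons.

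A reader might also infer that the SD itself is too small, because a span of 1 to 99% looks wide for an SD of 20. The documents do not support this. It would require treating that span as the observed range of about 25 normal values, which the text does not say. The expected range grows with sample size: for 80 to 90 normal values it is about 4.9 SD, and 98/4.9 = 20. The 20% is attributed to a cited source that cannot be examined here.

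**Conclusion.** The point holds as an inconsistency within one sentence. The stated 80% power at 16 points belongs to 25 analysed per group, while the sentence assumes that some values will be missing. At an SD of 20 and a two-sided 5% level, power at 16 points is about 74% by t-test (76% normal) if 3 are lost per group, and about 76% (78%) if 3 are lost in total. The difference detectable with 80% power is then about 17.3 (16.9) or 16.7 (16.4) points.

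This rests on reading the dispersion as an SD of 20 points and 25 as the number enrolled. If 25 is the evaluable number, the power claim is sound and only the enrolment figure is missing from the sentence.

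Severity is minor to moderate. It would be wrong to infer that the randomised comparison is seriously underpowered: in the least favourable reading, the detectable difference moves from the stated 16 to 17.3 points. The Discussion's general power claim is a secondary matter.

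**What to change.** Restate the sample size item in section 2.2 according to what was meant:

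- Losses per group: 25 enrolled and 22 evaluable per group, SD 20 points, two-sided 5% t-test, 80% power for a difference of 17.3 points (74% at 16).
- Losses in total: 50 enrolled and 47 evaluable across the two randomised groups, same SD and test, 80% power for a difference of 16.7 points (about 76% at 16).
- 25 already evaluable: say so and state the enrolled number, which is 28 per group if the 3 losses are per group. The present power claim can then stay.

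In each case, call the 20% an SD if that is what it is. In the Discussion, limit "each with appropriate statistical power" to placebo versus vitamin C.

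The first two options cost only wording and a slightly less favourable stated figure, with no extra patients. The third changes nothing if the larger enrolment was already intended; otherwise it means 3 more patients per group.
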